#### Serum inflammatory factor levels

Before and 7 days after treatment, nurses will draw 5 ml of fasting venous blood from patients in the morning and detect the proportion of inflammatory cells and the levels of inflammatory factors such as C-reactive protein (CRP), tumor necrosis factor (TNF)-α, interleukin (IL)-1, IL-2, IL-6, and IL-8, and procalcitonin (PCT) in peripheral blood.

#### The sputum excretion volume

For patients who can cough spontaneously, nurses will collect and record the amount of sputum that can be excreted in 24 h, and those with negative pressure suction will use a disposable sputum suction device to record the amount of sputum excreted after each treatment. Collection by trained nurses takes place daily at 8:00 am and ends at 8:00 am the next day. Less than 10 ml/24 h is a small amount of sputum, 10–150 ml/24 h is a moderate amount of sputum, and more than 150 ml/24 h is a large amount of sputum. The color and consistency of the sputum will also be recorded.

#### Time to the disappearance of pulmonary rales

Auscultation of pulmonary rales will be performed by an experienced respiratory physician before the treatment, 2 h after the daily treatment period, and at the end of the treatment without using auxiliary expectoration equipment.

#### Pneumonia status score

The pneumonia severity index (PSI) [20] grading and clinical pulmonary infection score (CPIS) [21] will be used for evaluation before treatment and after 7 days of treatment, and the worst value within 24 h was calculated on the 7th day. The PSI risk level is reduced by two levels to be markedly effective, reduced by one level is effective, and the level is not reduced or increased is invalid. The clinical therapeutic effects of the test group and the control group will be compared by (markedly effective + effective)/total number of cases × 100%.

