### Eligibility criteria {10}

Eligible participants will undergo laboratory and imaging examinations to confirm the diagnosis of viral pneumonia and to assess eligibility to participate in the study.

Patients who meet all the following enrollment criteria will enter this study after signing the informed consent: (1) age 18–80 years old; (2) hospitalized patients had pneumonia-related symptoms, computed tomography (CT) examination met the diagnostic criteria of pneumonia, and the etiology examination suggested a viral origin; (3) patients who can cooperate with various examinations during clinical research; (4) the patient participates voluntarily, and he/she or his/her family agrees and signs the informed consent.

Patients who meet the following criteria will be excluded: (1) other types of pneumonia, such as bacterial pneumonia, mycoplasma pneumonia, falling accumulation pneumonia, etc.; (2) patients with bronchiectasis or lung malignancies; (3) patients with chest skin injury who cannot wear the LIPUS device; (4) pregnant and breastfeeding women; (5) contraindications to the therapeutic ultrasonography (US), including dermatological conditions, local abnormal sensations in the chest or back, epilepsy, etc.; (6) patients with mental illness or unable to communicate normally with staff.

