## Assignment of interventions: allocation

### Sequence generation {16a} and concealment mechanism {16b}

Participants will be randomized into three groups (LIPUS group; control group; self-control group) in a ratio of 1:1:1 using a computer-generated randomization sequence. Research assistants not involved in clinical care or outcome assessment will prepare sequentially numbered, opaque, sealed envelopes based on the randomization list and ensure the confidentiality and independence of the allocation data. When appropriate, the assistant will open envelopes and ensure the coordination of therapeutic interventions.

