## Statistical methods

### Statistical methods for primary and secondary outcomes {20a}

Analysis of baseline characteristics of the three groups will be summarized by appropriate descriptive statistics. Analysis of both the primary and secondary outcomes will be performed blinded to treatment assignment and analyzed on the intention-to-treat approach [22], with all randomized participants retaining their original randomization group. If these missing data are judged to be random, multiple imputations of the chained equation will be used to address missing data caused by lost access and non-response.

Normally distributed data were expressed as the mean (standard deviation), whereas data not normally distributed was expressed as the median (interquartile range). The independent sample test was used for the comparison between groups, and the paired sample test was used for the comparison within the group before and after treatment. For clinical symptoms, variables were expressed as percentages. A *χ*^2^ test or Fisher’s exact test was used to compare categorical data. The conventional level of 0.05 for statistical significance was adopted to evaluate the *p*-values. Statistical analysis was carried out by using SPSS software, version 26.

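### Under the PSI response rule a patient who enters at the lowest risk level can never count as a responder, which dilutes the difference in response percentages

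*Protocol article*

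**What the plan says.** The section Pneumonia status score has PSI graded before treatment and after 7 days. A fall of two levels is markedly effective; for the remaining cases, "reduced by one level is effective, and the level is not reduced or increased is invalid". The section also fixes the summary measure and the denominator: "The clinical therapeutic effects of the test group and the control group will be compared by (markedly effective + effective)/total number of cases", expressed as a percentage.

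Four other places bear on the point.

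- Eligibility criteria {10} asks for adults up to 80 years. It further requires that "hospitalized patients had pneumonia-related symptoms, computed tomography (CT) examination met the diagnostic criteria of pneumonia, and the etiology examination suggested a viral origin". It names no minimum severity and no PSI level.
- Sequence generation {16a} describes allocation "in a ratio of 1:1:1 using a computer-generated randomization sequence" and mentions no stratification by baseline PSI.
- Statistical methods {20a} says that a χ² "test or Fisher’s exact test was used to compare categorical data". It states no baseline adjustment.
- Sample size {14} gives 66 participants allocated 1:1:1, raised to 70 for dropout.

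Nowhere does the article say how a patient who is already at the lowest level before treatment is to be counted.

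**The concern.** Any ordered scale has a lowest level, so no outside knowledge of PSI scoring is needed. A patient at that level before treatment has only two possible results, staying or rising, and the rule calls both invalid. The same patient remains in the denominator. Full recovery and no recovery are therefore recorded alike, and for these patients the outcome carries no information about treatment.

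The article fixes the cut-points, the denominator and the groups compared. This is therefore a stated rule that works badly, not a detail left to an analysis plan, and a plan that followed it would carry the problem forward. The resulting percentage would be read as a clinical effectiveness rate, although it depends partly on how severely ill the patients were at entry.

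**Working it through.** **Inputs.** From the article: the response rule, the all-cases denominator, no entry floor on PSI, significance level 0.05, a χ² or Fisher test, and 66 participants in three equal groups, so 66/3 = 22 per arm. The dropout step reproduces: 66/0.95 = 69.5, rounded up to 70. The 66 itself cannot be rebuilt, because no effect size or standard deviation is given. The article states no figure for the PSI outcome.

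Assumed, because the article gives neither: response of 70% (LIPUS) and 40% (control) among patients who can improve, and a share f of each arm at the lowest level.

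**Step 1, dilution.** Lowest-level patients contribute no responders but stay in the denominator. Each arm's rate is multiplied by 1 − f:

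- difference = (1 − f) × (70 − 40) points
- risk ratio = [(1 − f) × 70] / [(1 − f) × 40] = 1.75 for every f

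Power is by exact enumeration of the two-sided Fisher test at 22 per arm.

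| f | LIPUS | Control | Difference (points) | Fisher power |
|---|---|---|---|---|
| 0 | 70% | 40% | 30 | 40% |
| 5% | 66.5% | 38% | 28.5 | 36% |
| 10% | 63% | 36% | 27 | 32% |
| 20% | 56% | 32% | 24 | 25% |
| 40% | 42% | 24% | 18 | 16% |

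The χ² test shows the same pattern at a higher level: exact power is 52%, 44%, 36% and 24% at f = 0, 10%, 20% and 40%.

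**Step 2, the rate restricted to patients who can improve.** At f = 40% this leaves 22 × 0.6 = 13.2, taken as 13 per arm. The expected difference returns to 30 points and Fisher power is 26%, against 16% with all 22 in the denominator. Under this rule, leaving these patients out of the rate gives more power than keeping them in.

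**Step 3, chance imbalance.** The standard deviation of the between-arm difference in lowest-level share at f = 40% is √(2 × 0.4 × 0.6/22) = 0.148. With the same true response p in both arms, a one-standard-deviation imbalance shifts the observed difference by 0.148 × p: 5.9 points at p = 40% and 10.3 points at p = 70%.

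**Step 4, false positives overall.** With equal true response of 40%, 55% or 70% and f from 0 to 60%, exact Fisher type I error at 22 per arm stays between 2.2% and 2.4%. At 55% response the standard deviation of the observed difference is √(2 × 0.55 × 0.45/22) = 15.0 points at f = 0. At f = 40% the rate becomes 0.6 × 0.55 = 0.33, which gives √(2 × 0.33 × 0.67/22) = 14.2 points. The shift in step 3 is thus part of ordinary sampling error, which the test already allows for.

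**The case against.** The strongest counter-arguments concern reach, not the mechanism.

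- **False differences.** A reader might infer that the rule manufactures false positive results. It does not. Type I error averaged over randomisations stays near or below nominal (step 4), and chance imbalance in any prognostic factor moves any unadjusted comparison. What remains is conditional: in a trial where the arms happen to differ in lowest-level patients, the observed difference is shifted, and the planned test does not adjust for it.
- **Frequency.** A reader might infer that lowest-level patients will certainly be enrolled. The article requires hospitalised, symptomatic, CT-confirmed pneumonia and gives no baseline PSI distribution. The text supports only that they can be enrolled. At f = 5% the loss is 1.5 points, and at f = 0 it is nil.
- **Importance.** A reader might take this rate for a leading secondary outcome. The article lists pneumonia status score unranked among its secondary outcomes, does not name PSI in the objectives, and records a second score (CPIS) at the same times.
- **Scale and power.** The dilution applies to the difference in percentages and leaves the risk ratio alone. Power for this outcome is also low without the problem: 40% at best under the assumed rates. Both points stand. However, the percentage is the measure that the article specifies, and low power is no reason to lose more of it.
- **Intention to treat.** Taking patients out of a denominator may look at odds with the stated analysis of all randomised participants. A restriction on a value recorded before randomisation does not break the randomised comparison, but the wording must say that this is what is done.

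**Conclusion.** The point holds in a limited form. As written, the rule counts every patient who enters at the lowest PSI level as a treatment failure, and nothing in the article prevents such patients from entering or treats them differently. The difference in response percentages shrinks by the factor 1 − f. Under the assumed 70% against 40% and 22 per arm, the loss runs from 1.5 points and about 4 percentage points of Fisher power at f = 5% to 12 points and about 24 percentage points of power at f = 40%.

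The factor 1 − f follows from the rule alone. The power figures rest on assumed response rates, and the size in practice rests on f, which the article does not give. No inflation of overall type I error follows. Imbalance matters only in a trial where it occurs: about 6 to 10 points for a one-standard-deviation imbalance at f = 40%, for 40% to 70% response in both arms. One secondary outcome is affected; the primary CT outcome is not.

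**What to change.** Change the wording for this secondary outcome in one of two ways.

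1. Keep the response rate, but compute it among all randomised patients whose PSI level before randomisation is above the lowest. Stratify by baseline level where numbers allow, and report lowest-level patients separately as stayed or worsened. State that the restriction uses a pre-randomisation value, so that it agrees with the intention-to-treat statement in Statistical methods {20a}.
2. Alternatively, compare the day-7 PSI level between arms adjusted for baseline level, for example with a proportional-odds model, using all patients.

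Both PSI assessments are already planned, so no visit, measurement or sample size changes. The first option has a smaller denominator; the second may meet sparse levels with about 22 patients per arm. The choice should be fixed before allocation is revealed.

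### The PSI effective rate counts every participant who enters at the lowest risk level as a failure; if such patients enrol, this secondary comparison is diluted and loses power

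*Protocol article*

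**What the plan says.** Under Pneumonia status score, the protocol grades PSI before treatment and after 7 days and sorts participants by the change in level. Success has two grades: "The PSI risk level is reduced by two levels to be markedly effective, reduced by one level is effective". For the rest, "the level is not reduced or increased is invalid". The test and control groups "will be compared by (markedly effective + effective)/total number of cases", expressed as a percentage. No exception is made for a participant who is already at the lowest level.

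Under Eligibility criteria {10}, the disease requirement is that "hospitalized patients had pneumonia-related symptoms, computed tomography (CT) examination met the diagnostic criteria of pneumonia", together with an etiology work-up pointing to a virus. No minimum PSI level or other severity threshold appears among the inclusion or exclusion criteria.

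Under Statistical methods {20a}, a χ² "test or Fisher’s exact test was used to compare categorical data", and "The conventional level of 0.05 for statistical significance was adopted". No stratification or adjustment by baseline level is stated. The same section commits the primary and secondary outcomes to intention-to-treat, and section {20b} rules out subgroup analysis.

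**The concern.** On any ordered scale the bottom category cannot be lowered. A participant who enters at the lowest PSI level therefore has no route to success under this rule, yet remains in the denominator. The result would be reported as a therapeutic effect, although for these participants it was settled before treatment began.

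This is not a detail left to an analysis plan, because the success rule, the failure rule and the denominator are all fixed in the text. It is also separate from the pooling of one-level and two-level falls: the floor would remain if the change in level were analysed as an ordered variable.

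At stake are the size of the reported effective rate, the absolute difference between LIPUS and control, and the power of this one secondary comparison.

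**Working it through.** **The plan's own figure.** Sample size {14} gives 66 participants at 1:1:1, so 66/3 = 22 per group. With about 5% dropout, 66/0.95 = 69.5, which rounds up to the stated 70. (The Abstract says sixty, or 20 per group; I use 22.) No rate, effect or power is stated for the PSI outcome, so there is nothing further to reproduce.

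**Inputs**
- From the protocol: 22 per arm, the 0.05 level, and the success rule and denominator above.
- Assumed: f, the share of each arm entering at the lowest PSI level, and pT and pC, the true rates of a fall in level among participants with room to fall (LIPUS and control). The protocol gives none of these, so a range is shown.

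**Step 1: expected rates.** A share f has success probability 0 and a share (1 − f) has probability p, so the rate as written is (1 − f)p. The difference is (1 − f)(pT − pC) and the ratio is pT/pC. With pT = 80%, pC = 40% and f = 30%:
- LIPUS: 0.7 × 80% = 56%
- Control: 0.7 × 40% = 28%
- Difference: 28 points instead of 40
- Ratio: 2 in both cases

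**Step 2: power.** For each trial, lowest-level entrants were drawn as Binomial(22, f) in each arm and successes as Binomial among the rest. A pooled-variance two-proportion z test (equivalent to χ² without continuity correction) was applied at two-sided 0.05, once to all participants and once with lowest-level entrants removed. Each cell shows power as written / restricted, in %.

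| pT v pC | f = 0 | 5% | 15% | 30% | 50% |
|---|---|---|---|---|---|
| 80 v 40 | 79 / 79 | 74 / 79 | 63 / 73 | 47 / 65 | 30 / 51 |
| 80 v 50 | 55 / 55 | 49 / 55 | 40 / 50 | 29 / 43 | 18 / 33 |
| 70 v 35 | 66 / 66 | 61 / 65 | 52 / 59 | 38 / 51 | 26 / 39 |
| 50 v 20 | 55 / 55 | 52 / 55 | 46 / 50 | 37 / 43 | 26 / 33 |
| 30 v 10 | 39 / 39 | 37 / 37 | 33 / 34 | 27 / 28 | 18 / 20 |

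For f from 15% to 50%, restriction gains about 10–21 points at 80 v 40%, 4–6 at 50 v 20% and 0–2 at 30 v 10%. At f = 5% the gain is 0–5 points across these pairs, apart from just under 6 at 80 v 50%.

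**Step 3: cross-check.** A normal-approximation formula for 80 v 50% at f = 20% gives expected rates of 64 v 40%, with power 35.3% as written, 46.1% restricted and 55.3% with no floor. Fisher's exact test agrees in direction there (24.9% v 35.9%). In one low-rate case (50 v 20%, f = 30%) Fisher's power is slightly higher as written (26.4% v 24.6%), an effect of discreteness and of rounding the restricted arm to 15.

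**Step 4: type I error.** With 50% v 50% and f from 5% to 50%, rejection as written was 4.6–5.0%.

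**Step 5: chance imbalance.** With 22 per arm, the arms differ by four or more lowest-level entrants in about 14%, 25% and 29% of trials at f = 15%, 30% and 50%. With p = 50%, a gap of four moves the expected difference by 4 × 0.5/22 = 9 points in that trial.

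**The case against.** The consequence is conditional. The protocol gives no PSI distribution, and entry is limited to hospitalised, symptomatic patients with pneumonia on CT, so the share at the lowest level may be small. The power loss is also sensitive to response rates and is close to nil when these are low. All of this stands, and it is why the size is given as a range that starts at zero.

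The rate as written is a coherent quantity: the proportion of all cases whose level falls. It is too low only as a measure of response among those able to respond. That also stands.

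A reader might infer that the test is biased, or that an imbalance in lowest-level entrants would create a false treatment effect. The protocol does not support this. Type I error stays near 5%, and an imbalance in a baseline characteristic is part of the chance variation that an unadjusted test already allows for. It costs precision and does not add bias.

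A reader might also infer that a stated power is broken. Sample size {14} bases power on the primary outcome only. PSI is one of two pneumonia scores within one of several secondary outcomes, and the interpretation rules in the Discussion do not name it.

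Finally, restricting the rate removes randomised participants from it, which sits awkwardly with intention-to-treat and with the statement that there will be no subgroup analysis. This objection holds unless the text is reconciled, and the fix covers it.

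**Conclusion.** The defect follows from the wording alone: lowest-level entrants are failures by rule, they stay in the denominator, and nothing in the eligibility criteria keeps them out. If they make up a share f of each arm, the effective rates and their absolute difference shrink by the factor (1 − f), the ratio is unchanged, the test keeps its level, and power is lost.

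The amount cannot be fixed from the protocol. At 22 per arm, for response rates from 30 v 10% to 80 v 40%, the χ² power lost relative to a restricted rate runs from nil (f = 0) to about 2–21 points (f = 50%). The floor is certain, but its practical importance depends on who enrols. The protocol does not support saying outright that the rate will be understated and power lost. The point is worth correcting because it is cheap, but it touches one secondary outcome only and leaves the primary CT comparison as it is.

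**What to change.** Under Pneumonia status score, define the PSI effective rate among randomised participants whose baseline PSI level is above the lowest one, analysed in their randomised groups. Baseline level is measured before treatment, so the randomised comparison is preserved. For participants who enter at the lowest level, report the number per arm and the proportion still at that level on day 7.

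Alternatively, compare the day-7 PSI level as an ordinal outcome adjusted for baseline level, which keeps every randomised participant in the analysis.

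If the restricted rate is used, state in Statistical methods {20a} and Additional analyses {20b} that the restriction is part of the outcome definition, rests on a pre-randomisation characteristic, and is not a subgroup analysis.

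Counting stable lowest-level participants as successes is not a safe repair. It also dilutes the difference, and at 50 v 20% with f = 20% its power is 35.3%, against 42.3% for the rule as written (normal approximation).

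The cost is a few sentences and no new data, since PSI is already graded before treatment. The downside of the restricted rate is that fewer participants count in it. Rewording the two-level category as two or more levels is no part of this point, since both success categories are summed in the rate.

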#### The course of pneumonia

The hospitalization time and the time from the first symptom to discharge of the patients in each group will be counted. The discharge criteria for confirmed patients are as follows: (1) body temperature returned to normal for more than 3 days, (2) respiratory symptoms improved significantly, (3) pulmonary imaging showed significant improvement in acute exudative lesions, and (4) two consecutive viral antigen or nucleic acid tests were negative.

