### Secondary outcomes

Secondary outcome measures will be differences in the extent of lung inflammation dissipation on US images, pulmonary function, blood gas analysis, fingertip arterial oxygen saturation (SaO_2_) monitoring, serum inflammatory factor levels, the sputum excretion volume, time to the disappearance of pulmonary rales, pneumonia status score, and course of pneumonia.

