### Sample size {14}

Sample size and power calculation are based on the primary outcomes. All sample size calculations assume two-sided analysis with a power of 90% (1-*β* = 0.90) at a significant level of *α* = 0.05. The use of therapeutic LIPUS in viral pneumonia has not yet been reported. Based on the time span of this clinical trial and the number of patients expected to meet the inclusion criteria in our hospital, it is estimated that a total of 66 participants will be required (1:1:1 allocation ratio). We anticipate minimal missing data (< 5%) for the primary outcome (day 7 pulmonary inflammation on CT images) because participants were all inpatients and we have daily contact with them during the treatment phase. With a dropout rate of approximately 5%, a final sample size of 70 participants is required.

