### Recruitment {15}

Participants will be recruited from the Lingang Campus of Shanghai Sixth People’s Hospital Affiliated to Shanghai Jiaotong University School of Medicine, and they are all inpatients who have undergone laboratory and imaging examinations to confirm the diagnosis of viral pneumonia. The doctors will contact with the patients and their families, and after obtaining the informed consent from the patients themselves or their family members, doctors will conduct screening according to the inclusion and exclusion criteria. Only those who meet all recruitment requirements and do not meet any exclusion criteria will participate in this study.

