### Implementation {16c}

The sealed envelopes will be opened and reconcealed during the first LIPUS stage, before intervention by the staff responsible for randomization. The code will then be notified to the LIPUS experimenter.

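### Both course-of-pneumonia durations start before randomisation and are compared without adjustment, which can cost precision in this secondary outcome

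*Protocol article*

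**What the plan says.** The Secondary outcomes section of the protocol article ends its list with "time to the disappearance of pulmonary rales, pneumonia status score, and course of pneumonia". The section on the course of pneumonia then defines that outcome by two durations. The first is hospitalisation time; for the second, it says that "the time from the first symptom to discharge of the patients in each group will be counted". The second starts at symptom onset. The start of the first is not spelled out; admission is the ordinary meaning.

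Three other sections show where randomisation falls on those clocks:

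- Eligibility criteria {10} requires that "hospitalized patients had pneumonia-related symptoms, computed tomography (CT) examination met the diagnostic criteria of pneumonia". It sets no maximum number of days since onset or since admission.
- Recruitment {15} says of participants that "they are all inpatients who have undergone laboratory and imaging examinations to confirm the diagnosis of viral pneumonia".
- Implementation {16c} states: "The sealed envelopes will be opened and reconcealed during the first LIPUS stage, before intervention by the staff responsible for randomization".

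For the analysis, Statistical methods {20a} says: "The independent sample test was used for the comparison between groups". No covariate is named, and the text gives no duration counted from randomisation or first treatment.

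**The concern.** Treatment can act only on days after allocation. A duration that begins at onset or admission is the sum of a part fixed before allocation and a part that LIPUS might shorten. The treatment effect on the sum, in days, equals the effect on the second part alone, but the variance is that of the sum. If the two parts are unrelated, the variance rises and power falls. With small arms, one group may also happen to enter later in the illness, and that difference passes into the comparison of total duration.

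Reporting hospital stay alongside illness duration does not remove the difficulty, because on its ordinary reading that clock also starts before allocation. At stake is how informative this secondary outcome will be about whether LIPUS shortens the illness.

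**Working it through.** **Inputs from the protocol article.** Sample size {14} gives 66 participants at 1:1:1, two-sided alpha 0.05 and 90% power. Hence 66 / 3 = 22 per arm. The dropout step reproduces: 66 / 0.95 = 69.5, rounded up to 70. That sample size is based on the primary CT outcome and comes with no effect size or SD. No figure is stated for the course of pneumonia, so there is nothing of the plan's own to reproduce for this outcome.

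**Assumed inputs (not in the documents).** SD of time from randomisation to discharge, 4 days; true difference, 3 days; SD of pre-randomisation time, 3, 4 or 5 days; correlation rho between the two parts, varied.

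**Step 1: variance of the total.** Var(total) = SDpost² + SDpre² + 2·rho·SDpre·SDpost. With rho = 0:

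- SDpre 3: 16 + 9 = 25, ratio 25/16 = 1.56, SD 5.00
- SDpre 4: 16 + 16 = 32, ratio 2.00, SD 5.66
- SDpre 5: 16 + 25 = 41, ratio 2.56, SD 6.40

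**Step 2: power.** Two-sample t test, 22 per arm, difference 3 days. With the clock started at randomisation (SD 4), power is 68%.

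| SDpre (days) | Power, rho = 0 | Power, rho = -0.3 | rho at which the loss is zero |
|---|---|---|---|
| 3 | 49% | 64% | -0.375 |
| 4 | 40% | 54% | -0.50 |
| 5 | 33% | 44% | -0.625 |

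The last column solves SDpre² + 2·rho·SDpre·SDpost = 0, so rho = -SDpre / (2·SDpost): -3/8, -4/8, -5/8. Below these values the sign reverses. With SDpre 3 and rho = -0.5, the variance is 16 + 9 - 12 = 13, the SD is 3.61, and power is 77% on the present definition against 68% from randomisation.

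**Step 3: the same check without assuming days.** Normal approximation: 22 per arm gives 90% power for a standardised difference of (1.960 + 1.282)·√(2/22) = 0.977. Take that as the effect in units of SDpost. For SDpre/SDpost of 0.25, 0.5, 0.75 and 1.0, power becomes:

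- rho = 0: 88%, 83%, 74%, 63% (restoring 90% needs 24, 28, 35 or 44 per arm)
- rho = +0.3: 84%, 74%, 63%, 52%
- rho = -0.3: 92%, 91%, 87%, 78%

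**Step 4: chance imbalance.** The difference between two arms in mean pre-randomisation time has SD = SDpre·√(2/22), which is 0.9, 1.2 or 1.5 days for SDpre of 3, 4 or 5.

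**Step 5: what adjustment does.** Let P be days from onset to randomisation, D days from randomisation to discharge, A the arm, and T = P + D. If D = a + b·A + c·P + e, then T = a + b·A + (c + 1)·P + e. The coefficient b and the residual are identical for both clocks. The residual SD is SDpost·√(1 - rho²), which never exceeds 4 here. In the reversed case of step 2 (rho = -0.5) it is 4·√0.75 = 3.46, below both 3.61 and 4. Apart from about one degree of freedom, adjustment costs no precision whatever the correlation.

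**The case against.** The strongest reply is that the documents cannot show which time origin is more precise. The protocol describes recovery as mainly self-limiting, and discharge depends on milestones such as sustained normal temperature and repeated negative tests. These may follow the stage of illness, so patients who enter later could have fewer days left. That is negative correlation, and step 2 shows it can erase or reverse the loss. Moving the clock alone also leaves imbalance in illness stage able to affect the remaining stay. This objection stands: it limits the size of the loss and shows that adjustment matters more than the choice of origin.

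Four further points are fair:

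- The admission start is inferred, and the SDs of 3 to 5 days have no separate support for the interval from admission to randomisation, which cannot be longer than the interval from onset if symptoms came before admission.
- Total illness length and total stay are legitimate, readable measures.
- A covariate may be left to an analysis plan that is not shown, so its absence is not an omission in itself. The point is that the protocol does fix the start of the onset clock and does state an unadjusted comparison.
- A reader might infer that a stated objective is compromised. Shortening the disease course appears in the background rationale; the listed primary and secondary objectives do not name it, and no power was claimed for it.

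A reader might also infer systematic bias. The documents do not support that, because pre-randomisation time is balanced in expectation by randomisation.

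**Conclusion.** The point holds as a minor one about precision. The onset clock certainly includes pre-randomisation time, and the hospital clock does on its ordinary reading. Nothing in eligibility limits that time, and the stated test does not adjust for it. Under the assumed 4-day SD and 3-day effect, the loss runs from 68% power down to 49%, 40% or 33% when the two parts are independent. It shrinks with negative correlation and is zero at rho of about -0.38, -0.50 or -0.63. None of the SDs, the effect or the correlation comes from the documents, so these figures show a range of possibilities and do not estimate what this trial will lose. It would be wrong to conclude that the present definition always adds net noise. The primary CT outcome and the stated sample size are not affected.

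**What to change.** Define the between-group duration as days from randomisation (the first session) to discharge. Compare the groups in a model that includes days from symptom onset to randomisation and, for hospital stay, days from admission to randomisation. Report both intervals by group as baseline variables. State that hospitalisation time starts at admission, if that is what is meant, and keep the two present durations as supplementary measures.

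The cost is a change of wording and one or two model degrees of freedom. Onset, admission and discharge dates are needed for the present outcome, and the randomisation date is known, so no visit, test or participant is added.
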